#### Secondary acceptability and feasibility outcomes

Recruitment into the trialParticipant and PWP acceptability and satisfaction of smoking cessation treatment (Modified version of the Stop Smoking Service Client Satisfaction Survey [32] and Modified version of a clinician self-report intervention acceptability questionnaire [33])Qualitative interviews with PWPs will explore PWP perceptions of:Acceptability of the smoking cessation treatmentAcceptability of data collection proceduresPositive and negative impacts of smoking cessation treatment on IAPT usual care and mental health recoveryQualitative interviews with participants will explore participant perceptions of:PWP ability to deliver the smoking cessation treatmentAcceptability of the smoking cessation treatmentPositive and negative impacts of smoking cessation treatment on IAPT usual care and mental health recovery

#### Implementation outcomes

*Intervention Implementation Checklist*: We will listen to a proportion of smoking cessation treatment sessions and note which intervention components were delivered or not (Table 2)Observations and listening to intervention delivery recordings

#### We will check data completeness for the following outcomes

Smoking-related:Carbon monoxide (CO)-verified 7-day point prevalence smoking cessation (i.e., validated by exhaled carbon monoxide concentration of < 10 ppm (ppm) [34]. CO-testing will be available on both sites via a 3 month follow-up home visit.Number of cigarettes per day (CPD)Heaviness of Smoking Index (HSI) [35]

Mental health-related:Patient Health Questionnaire (PHQ-9) [36] score

Service-related:Number of ‘Did Not Attends’Number of planned, completed and missed IAPT appointments

### Sample size

#### Trial

Assuming a sample size of 100 participants at follow-up, we used a standard formula to calculate the binomial exact confidence interval [37, 38]. The study will have sufficient power to estimate that 40% or more participants will continue with smoking cessation treatment in the intervention arm with a 95% confidence interval of 26% to 55% (i.e., assuming the true rate is 40%).

Therefore, assuming that about 36% of participants will be lost to follow-up [39], this study will require a sample size of 157 at baseline:$$ \left(\mathrm{i}.\mathrm{e}.,157-\left(157\ \left(\frac{36}{100}\right)\right)=100\right)\Big) $$

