**Discussion:**

If the intervention is shown to be acceptable, feasible and suitably implemented, we can conduct a randomised controlled trial. In a future trial, we would examine whether adding smoking cessation treatment increases smoking abstinence and improves depression and anxiety more than usual care, which would lead to long-term health improvement.

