### Randomisation and intervention assignment methods

#### Sequence generation

The randomisation sequence will be generated by a statistician using Stata software. Randomisation will be stratified by site and blocked, and participants will be randomised using a 1:1 algorithm to ensure an equal number of participants in the treatment and control arms.

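### The sample-size paragraph presents a precision calculation as power: an exact interval of 26% to 55% around an assumed 40% cannot establish that 40% or more continue treatment

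*Protocol article*

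**What the plan says.** The Sample size section (Trial) of the protocol article starts from the number expected at follow-up: "Assuming a sample size of 100 participants at follow-up, we used a standard formula to calculate the binomial exact confidence interval". It then draws this conclusion: "The study will have sufficient power to estimate that 40% or more participants will continue with smoking cessation treatment in the intervention arm". The same sentence gives a 95% confidence interval of 26% to 55% and qualifies it with "i.e., assuming the true rate is 40" per cent. The next paragraph inflates the 100 to 157 at baseline, "assuming that about 36% of participants will be lost to follow-up".

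The section gives no null rate and no power value. Under Sequence generation, "participants will be randomised using a 1:1 algorithm to ensure an equal number of participants in the treatment and control arms", so 100 at follow-up means about 50 per arm.

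The proportion in question is the main acceptability and feasibility outcome. On what follows from the results, the Abstract (Discussion) says only: "If the intervention is shown to be acceptable, feasible and suitably implemented, we can conduct a randomised controlled trial".

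**The concern.** The sentence makes two claims that the calculation does not support. One is about power, which has no meaning without a rate to be excluded and a true rate at which to exclude it. The other is directional, that the rate is at least 40%. An interval centred on 40% has roughly half its length below 40%, so it cannot support that direction.

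What is at stake is how the main outcome is read. 40% is the only figure that the article attaches to retention in treatment. A reader could take an observed 40% (26% to 55%) as confirming a level that the study was designed to demonstrate, when the same data are compatible with only about a quarter of participants continuing. The article's caution about imprecision, under Piloting main trial outcomes, concerns the estimated intervention effects and does not cover this proportion.

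**Working it through.** **Inputs**
- 100 participants at follow-up, an assumed true rate of 40%, a 95% exact binomial interval and 36% loss to follow-up (Sample size, Trial).
- 1:1 allocation (Sequence generation), giving 100/2 = 50 in the intervention arm.

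**Step 1: reproduce the plan's figures.** For x successes in n, the exact (Clopper-Pearson) limits are the 0.025 quantile of Beta(x, n − x + 1) and the 0.975 quantile of Beta(x + 1, n − x).
- x = 0.40 × 50 = 20 gives 26.4% to 54.8%, which is the printed 26% to 55%.
- For comparison, 40/100 gives 30.3% to 50.3%, and the Wald interval for n = 50 is 26.4% to 53.6%. The printed figure is therefore the exact interval for one arm of 50.
- Baseline size: 100/(1 − 0.36) = 156.25, rounded up to 157. Check: 157 × 0.64 = 100.48.

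Both stated figures are correct from their inputs.

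**Step 2: what the interval says about 40% or more.** The lower limit lies 40 − 26.4 = 13.6 points below 40%. With the result that the plan itself assumes, true rates down to about 26% are not excluded.

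**Step 3: what establishing more than 40% would take with n = 50.** Find the smallest x whose lower exact 95% limit exceeds 40%:
- 27/50: 39.3% to 68.2%, not enough.
- 28/50 (56%): 41.3% to 70.0%, enough.

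The power of that requirement is P(X ≥ 28) with X ~ Binomial(50, p):

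| True rate p | P(X ≥ 28) |
|---|---|
| 45% | 8% |
| 50% | 24% |
| 55% | 50% |
| 60% | 77% |
| 65% | 93% |

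Solving P(X ≥ 28) = 0.80 gives p = 60.8%, or about 61%. With a one-sided 95% limit the cut falls to 27/50 (54%), with power of 34% at a true 50% and 84% at a true 60%.

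**Step 4: sensitivity to the denominator.** Main acceptability and feasibility outcome, and Primary and secondary feasibility measures, both divide by the number randomised. That is 157/2, about 78 per arm.
- Precision: 31/78 (39.7%) gives 28.8% to 51.5%, or about 29% to 51%.
- Lower limit above 40%: 40/78 gives 39.7% (not enough) and 41/78 (53%) gives 40.9% (enough). Power for 41/78 is 37%, 71% and 93% at true rates of 50%, 55% and 60%. It reaches 80% at about 57%.

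The larger denominator narrows the interval, but its lower end is still about 11 points below 40%. The conclusion does not depend on which denominator is used.

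**The case against.** The strongest reply is that precision was plainly meant. The section names an exact confidence interval as its method, prints the interval with its 26% lower end in the same sentence, states the assumed true rate, and speaks of estimating rather than of testing. No number is wrong and nothing is hidden. This stands as a reading of intent, and it is why the sample size is not in question. It does not rescue the wording, because a precision statement needs neither a claim of power nor a direction.

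A reader might infer that 40% is the success criterion for going on to a full trial, so that the study is set up to make a wrong progression decision. The article does not support that. It attaches no threshold to the main outcome, and the condition in the Abstract is qualitative and broader than retention. Any formal progression rule could be in documents not shown here.

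A reader might also point out that, at a true rate of 40% with n = 50, the lower limit exceeds 40% with probability only 1.6%, and that the observed rate reaches 40% only 55% of the time. Both are correct, but neither counts against this design. A 95% interval lies wholly above the true value about 2.5% of the time or less at any sample size, and an estimate falls on either side of the truth about half the time. The informative figures are the count needed (28/50) and the true rate needed for 80% power (about 61%). Those too describe a test that the plan does not pose. They show only what the claim of power would require.

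**Conclusion.** The point holds as a fault of wording and inference. The sentence ascribes to the study a property that its calculation does not provide: an exact interval of 26% to 55% around 40% gives no power to establish 40% or more. With 50 in the intervention arm, at least 28 (56%) would have to continue, and the true rate would have to be about 61% for an 80% chance of that. These figures assume a two-sided exact 95% limit and 50 participants in the arm. With about 78 in the arm, the corresponding figures are 41/78 (53%) and about 57%.

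This is not an arithmetic error, since the interval and the 157 both reproduce. Nor does it show that a decision rule is flawed, because the article states no rule at 40%. The consequence is limited to overstated certainty about the main outcome.

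**What to change.** In Sample size (Trial), delete the words *sufficient power* and *or more*, and put a precision statement in their place. For example: if 40% of intervention-arm participants continue with smoking cessation treatment, the proportion will be estimated with an exact 95% confidence interval of 26% to 55% (20/50).

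If the proportion is to be reported over all randomised participants, as the outcome definition has it, give the matching interval of about 29% to 51% (31/78). Whichever denominator is used, name it beside the interval.

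Do not present 40% as a powered target here or in the report of results. If the sponsor does want to show that retention exceeds 40%, the section must state the rate to be excluded, an assumed true rate above it and the resulting power.

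The cost is one reworded sentence. Sample size, outcome, analysis and conduct are unchanged, and the stated claim becomes more modest.

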#### Quantitative data collection

Table 1 and Fig. 1 present a schedule of data collection. Most participant data will be collected as part of usual care. Baseline and 3 month follow-up data will be collected by a researcher. Usual care data will be recorded by PWPs using patient management software and then extracted and input into RedCap by researchers (Table 3).

**Table 3 Tab3:** List of variables, and who the variables will be collected by

Category	Variable	Collected by who*	Are data collected as part of routine care?
Eligibility	Eligibility criteria met	Researcher	No
Demographics	Date of birth	PWP/researcher	Yes
	Ethnicity	PWP/researcher	Yes
	Gender	PWP/researcher	Yes
	Education	PWP/researcher	Yes
Mental health	Comorbid mental health conditions	PWP/researcher	Yes
	PHQ-9	PWP/researcher	Yes
	GAD-7	PWP/researcher	Yes
Smoking	Smoking status	PWP/researcher	Yes, but not regularly
	Smoking history	PWP/researcher	No
	Cigarettes per day	PWP/researcher	No
	Bio-verification of smoking status	Researcher	No
	Smoking cessation medication used in intervention	PWP	No
Service	Participant drop-out of IAPT	PWP	Yes
	Planned, completed and missed IAPT appointments	PWP/researcher	Yes
Acceptability and feasibility	Retention in smoking cessation intervention	PWP	No
	Participant satisfaction with smoking cessation intervention	PWP/researcher	No
	Clinician satisfaction with smoking cessation intervention	Researcher	No
	Qualitative Interviews	Researcher	No
Implementation	Audio recording of treatment session	PWP	Yes
	Intervention implementation checklist	Researcher	No

**PWP* = Psychological wellbeing practitioner

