#### Primary and secondary feasibility measures

We will present the number of participants who were screened, randomised, treated, and followed up for primary outcome in a CONSORT-style flow chart. The proportion of study completers, by trial arm, will be calculated as:$$ \frac{N\ \mathrm{study}\ \mathrm{completers}}{N\ \mathrm{randomised}\ \mathrm{at}\ \mathrm{baseline}} $$

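### The stated precision for the main outcome (26% to 55%) is calculated on about 50 followed-up intervention participants, but the outcome is defined on all 78 or 79 randomised to that arm

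*Protocol article*

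**What the plan says.** All references are to the protocol article.

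- **Sample size, Trial.** The calculation starts from a follow-up number: "Assuming a sample size of 100 participants at follow-up". For the method, "we used a standard formula to calculate the binomial exact confidence interval". The target is 40% or more continuing with treatment "in the intervention arm with a 95% confidence interval of 26% to 55"%, "assuming the true rate is 40"%. The next paragraph inflates for attrition: "assuming that about 36% of participants will be lost to follow-up [39], this study will require a sample size of 157 at baseline".
- **Main acceptability and feasibility outcome.** A completer is someone who stays in the smoking cessation treatment until they stop smoking, make a quit attempt or finish IAPT care. Attending the 3-month follow-up is not part of the definition. The displayed formula divides completers by the number randomised at baseline.
- **Primary and secondary feasibility measures.** The same formula and denominator are printed again: "The proportion of study completers, by trial arm, will be calculated as" completers over number randomised.
- **Quantitative data collection, Table 3.** The row "Retention in smoking cessation intervention" names the psychological wellbeing practitioner (PWP, the therapist) as sole collector. The text of that section says that a researcher collects the 3-month data.
- **Sequence generation.** "participants will be randomised using a 1:1 algorithm to ensure an equal number of participants in the treatment and control arms".

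**The concern.** The sample-size paragraph and the outcome definition use different denominators for the same quantity. The first counts intervention participants reached at follow-up. The second counts everyone randomised to the intervention. Completion is judged from treatment attendance and recorded by the therapist, so a participant whom the researcher cannot reach at 3 months stays in the printed denominator and can still be a completer. Loss to follow-up is therefore not the mechanism that reduces the sample size for this outcome, yet the inflation from 100 to 157 is attached to it.

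Two things are at stake. First, the only precision statement given for the main outcome does not describe the estimate that the trial will report. Second, the paragraph does not say whether the 40% planning value describes all those randomised or only those followed up. The two readings lead to clearly different expected results on the defined denominator, and a reader who compares the eventual result with 40% needs to know which was meant.

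**Working it through.** **Inputs**

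- Total at follow-up: 100, both arms together (Sample size, Trial).
- Assumed rate: 40%; exact binomial 95% interval (Sample size, Trial).
- Loss to follow-up: 36%; baseline total: 157 (Sample size, Trial).
- Allocation 1:1 (Sequence generation). This gives 100/2 = 50 followed up per arm and 157/2 = 78.5, so 78 or 79 randomised per arm. The protocol does not print these per-arm figures; they are derived.
- Outcome denominator: number randomised (both statements of the formula).

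**Formula.** The exact (Clopper-Pearson) 95% limits for x completers out of n are:

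- lower = 2.5% quantile of Beta(x, n − x + 1)
- upper = 97.5% quantile of Beta(x + 1, n − x)

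**Step 1: reproduce the protocol's figures**

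| Completers / n | Proportion | Exact 95% interval | Matches 26% to 55%? |
|---|---|---|---|
| 20/50 | 40.0% | 26.4% to 54.8% | Yes |
| 40/100 | 40.0% | 30.3% to 50.3% | No |

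Baseline total: 100/(1 − 0.36) = 100/0.64 = 156.25, rounded up to 157. This matches. Both printed figures reproduce, and the interval identifies n = 50, the followed-up half of the intervention side.

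**Step 2: use the defined denominator, if 40% applies to all randomised**

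| Completers / n | Proportion | Exact 95% interval | Width |
|---|---|---|---|
| 31/78 | 39.7% | 28.8% to 51.5% | 22.6 points |
| 32/79 | 40.5% | 29.6% to 52.1% | 22.5 points |

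The stated interval (20/50) is 54.8 − 26.4 = 28.4 points wide. The defined outcome would be estimated with an interval about 6 points narrower. On this reading, 26% to 55% would need only 2 × 50 = 100 randomised, with no inflation.

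**Step 3: use the defined denominator, if 40% applies only to those followed up and losses count as non-completers**

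Expected completers: 0.40 × 50 = 20. As a proportion of those randomised: 0.40 × 0.64 = 25.6%.

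| Completers / n | Proportion | Exact 95% interval |
|---|---|---|
| 20/78 | 25.6% | 16.4% to 36.8% |
| 20/79 | 25.3% | 16.2% to 36.4% |

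On this reading the interval for the defined outcome excludes the 40% planning value.

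**The case against.** The case on the other side is substantial, and much of it stands.

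- *The arithmetic is right.* Both printed figures reproduce. The fault is a mismatch of denominators, not a miscalculation.
- *The mismatch is conservative.* If 40% applies to all randomised, the trial will be somewhat more precise than stated and recruitment is not too small. This limits the severity, but it does not make the stated interval the right one, and it does not hold on the reading in Step 3.
- *157 is defensible.* The study also aims to test data collection and to pilot the main-trial measures by arm at 3 months. A 36% allowance is reasonable for those outcomes. The difficulty is that the paragraph derives 157 from the retention interval and mentions no other outcome.
- *Some loss on this outcome may have been foreseen.* The analysis section describes its flow chart as including those followed up for the primary outcome, participants may withdraw their data, and Table 3 marks retention as not routinely collected. Planning on 50 could be a cautious floor. The protocol does not say so, and the formula directly after the flow-chart sentence still divides by all randomised.

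A reader might infer something stronger: that the analysis will be run on the 50 followed up and will overstate retention. In the extreme, if all 28 of 78 lost were non-completers and were left out, 31/78 (40%) would become 31/50 (62%). The documents do not support this. The randomised denominator is printed twice, once in the analysis section itself, and the sample-size paragraph prescribes no analysis denominator. That scenario needs both a departure from explicit text and the worst possible pattern of loss, so it is no argument for severity.

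Nor is a rule for unknown retention missing. With completers over all randomised, anyone not shown to be a completer already counts as a non-completer, and further detail can be left to the statistical plan that the protocol promises.

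**Conclusion.** The point holds as an internal inconsistency of moderate severity. The 26% to 55% interval describes 20 of 50 followed-up participants; the main outcome is defined on 78 or 79 randomised. The interval that the defined outcome will have depends on something the protocol leaves open:

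- about 29% to 52% if the 40% refers to all randomised, in which case the stated interval is too wide by about 3 points at each end;
- about 16% to 37%, around an expected 26%, if the 40% refers to those followed up and losses count as non-completers.

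Neither reading shows that 157 is too few. The conclusion assumes equal allocation, so 50 followed up and 78 or 79 randomised in the intervention arm, and that therapist records of retention do not depend on the 3-month researcher contact, as Table 3 indicates.

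**What to change.** Keep 157 and keep the number randomised as the denominator. In the sample-size paragraph:

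1. State whether the 40% refers to everyone randomised to the intervention or only to those followed up.
2. Replace the interval accordingly. If all randomised, give about 29% to 52% (31/78 or 32/79). If only those followed up, with losses counted as non-completers, give an expected proportion of about 26% with interval 16% to 37% (20/78).
3. Say that the 36% allowance serves the 3-month outcomes, leaving about 100 in total and 50 per arm.

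The cost is one restated figure and one or two sentences, with no change to recruitment, data collection or the analysis formula. It is best settled before the data are analysed, so that the meaning of the 40% is fixed without knowledge of the result.

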#### Interviews

We will aim to interview all PWPs who deliver the smoking cessation treatment and 20 trial participants, or until saturation is reached [40]. We will use a purposeful sampling method and aim for variation across the sites and participant final smoking status.

### Recruitment and consent procedures

#### Trial

Researchers will search for potentially eligible participants via patient management software. Potentially eligible participants will be posted study information at least 2 weeks prior to their first IAPT appointment and contacted by a researcher before their first IAPT appointment to discuss eligibility and gain oral informed consent. The trial consent form is available in the Additional file 1.

#### Audio recording of treatment sessions

Sessions are recorded as part of IAPT usual care, and written informed consent is gained on the same day as treatment by PWPs.

#### Interviews

During the 3 month follow-up, trial participants will be recruited into interviews. PWPs involved in intervention delivery will be recruited into interviews after they have finished delivering the smoking cessation intervention to their final participant. Written or oral informed consent will be obtained on the day of the interview.

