### Setting

This is a multicentre study involving two Improving Access to Psychological Therapies (IAPT) sites in the UK (i.e., Bristol and Oxford). IAPT is a NHS primary-care based psychological therapy service (https://www.england.nhs.uk/mental-health/adults/iapt/). IAPT offers low- and high-intensity evidence-based therapies (e.g., cognitive behavioural therapy (CBT)) to people with common mental disorders. Psychological treatment is delivered by therapists named ‘psychological wellbeing practitioners’ (PWPs) and usually consists of six 30–45-minute sessions, delivered over the telephone or face-to-face (further details below).

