### Withdrawal of participants

Patient and PWP participants can withdraw from the study at any time, and they can withdraw their data from the study at any time during the study period.

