### PWP training programme

A maximum of ten PWPs per site will be trained to deliver the treatment. PWPs will take part in the following training:NCSCT level 1 online training and assessment programmeNCSCT level 2 face-to-face trainingAn overview about the importance of randomised trial methodology and study procedures (e.g., data recording)A researcher will visit each service once a month to listen in sessions and offer feedback to PWPs

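### Therapist interviews are limited to those who deliver the treatment and timed after their final participant, so interview-based acceptability may be biased upwards, by an unknown amount

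*Protocol article*

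**What the plan says.** The Outcomes section of the protocol article lists acceptability of the treatment and of the data collection procedures, as PWPs and participants see it, among the aims. The Abstract's discussion makes a later randomised trial conditional on the intervention proving acceptable, feasible and suitably implemented.

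Two sections define the PWP interviews:

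- Sample size, Interviews, sets the frame: "We will aim to interview all PWPs who deliver the smoking cessation treatment and 20 trial participants, or until saturation is reached".
- Recruitment and consent procedures, Interviews, sets the timing: "PWPs involved in intervention delivery will be recruited into interviews after they have finished delivering the smoking cessation intervention to their final participant".

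Three other sections bear on who might be left out:

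- Withdrawal of participants: "Patient and PWP participants can withdraw from the study at any time". No exit interview is described.
- PWP training programme: "A maximum of ten PWPs per site will be trained to deliver the treatment". The Setting section gives two sites.
- Primary and secondary feasibility measures: the flow chart will show "the number of participants who were screened, randomised, treated, and followed up for primary outcome", which describes trial participants, not therapists.

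Interviews are not the only source of PWP views. Secondary acceptability and feasibility outcomes also names a "Modified version of a clinician self-report intervention acceptability questionnaire", and Table 3 lists clinician satisfaction as a separate item collected by the researcher.

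**The concern.** Membership of the interview sample depends on having delivered, and the approach comes only when delivery has ended. A PWP may decline to deliver after training, or give up part-way, because the treatment does not fit the appointment. That PWP's view bears directly on acceptability, and the plan has no step that is sure to collect it. This is a survivor problem built into the sampling rule. It cannot be repaired at analysis, because views that were not collected cannot be recovered.

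Two features make it matter here. First, the group is small, so losing a few dissenting voices can change the themes. Second, the sites differ in a way that may affect PWPs' willingness to continue. Under Duration and number of sessions, Bristol PWPs fit the treatment into the usual appointment, while Oxford PWPs receive extra time. Sensitivity analyses plans to compare the two approaches for acceptability and feasibility. If more PWPs stop at one site, interviews with those who remain could blur that comparison.

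**Working it through.** The protocol states no target or figure for PWP acceptability, so there is nothing to reproduce. The check sets the sections side by side.

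**1. Size of the group.** At most ten trained PWPs per site and two sites give 10 × 2 = 20 trained PWPs at most.

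**2. Who is in the interview frame.**

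| PWP's history | Frame (Sample size, Interviews) | Timing (Recruitment and consent, Interviews) | Result |
|---|---|---|---|
| Trained, delivered, finished with last participant | In | Trigger occurs | Interviewed, if willing |
| Trained, delivered, then stopped after completing a participant | In, as one who delivered | That participant can be read as the final one | In frame; approach depends on the stop being noticed |
| Trained, withdrew or left with a participant in progress | In, as one who delivered | Has not finished with that participant; no trigger clearly applies | May be missed |
| Trained, never delivered | Out | No final participant; trigger never occurs | Excluded |

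Only the last row is excluded by rule. The third row is a risk created by the timing rule together with the absence of an exit step. The saturation clause in the frame, if it applies to PWPs as well as participants, can only shorten the list of interviewees.

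**3. What the other source covers.** The clinician questionnaire is listed under acceptability of and satisfaction with the treatment. Its respondents and timing are not restricted in the readable text, and the schedule in Table 1 is not shown. PWPs' views on data collection procedures, and on positive and negative effects on usual care and recovery, are listed only as PWP interview topics. For those topics no second PWP source is described.

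**4. Direction and size.** Bias arises only if both conditions hold: some trained PWPs are missed, and their views differ from those of the PWPs reached. If those missed are on average less favourable, the interviews look too favourable. If nobody is missed, or views do not differ, there is no bias. The protocol gives neither the number likely to be missed nor how their views might differ. Under Qualitative analysis the interviews are analysed thematically and yield no percentage, so no numerical size can be attached.

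**The case against.** The case on the other side has four parts.

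- **There is a second source.** A reader might infer that therapist acceptability is sought only from those who deliver and finish. The documents do not support that. The Abstract names questionnaires as well as interviews, and nothing readable limits the questionnaire to PWPs who deliver or to the end of delivery. This stands, and it confines the point to the interviews.
- **PWPs who stop are not excluded by rule.** The aim covers all who deliver, and a PWP who delivered and then stopped did deliver. This also stands. For that group the risk is practical: they may be gone, or no approach may be triggered.
- **The frame fits the aim.** The target is the treatment as delivered alongside usual care, and a PWP who never delivered has no experience of delivering it. Non-delivery may also be neutral, for example when no participant in the intervention arm was allocated to that PWP. The interview topics do include negative impacts. This stands in part: non-delivery cannot be read as rejection. However, the protocol does not record the reason, so neutral and unfavourable non-delivery cannot be told apart.
- **Therapist counts are reporting detail.** An article may leave them to the full protocol, and Fig. 1 and the additional file are not shown. This stands for the flow chart taken alone. It does not answer the interview rule, which two sections of the article state consistently.

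A reader might also infer that acceptability is overstated, or put a percentage on it. That would need invented numbers of missed PWPs and invented views, applied to interviews that produce no proportion.

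**Conclusion.** The point holds as a limit on the interviews. Trained PWPs who never deliver are outside the frame, and those who withdraw or leave part-way may be missed, although withdrawal is expressly allowed. Interview-based acceptability may therefore be biased upwards, most clearly on harm to usual care and on data collection, where the interviews are the only described source of PWP views. The size is unknown and may be zero.

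The conclusion rests on two assumptions: that some of the PWPs trained (at most 20) will not deliver or will not finish, and that their views are on average less favourable. Neither is established by the documents, but the protocol as written would not reveal whether either is true. The two sections do not contradict each other. This is a design choice that should be changed because it weakens evidence for a stated aim and is cheap to correct.

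**What to change.** Change both Interviews sections so that every trained PWP is invited to interview at the earliest of:

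- finishing with the last participant;
- withdrawal from the study;
- leaving the service;
- close of recruitment without having delivered.

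Record the reason for not delivering or for stopping, so that neutral reasons can be separated from objections to the treatment. Give the existing clinician acceptability questionnaire to the same group and say so in the text. Report by site the numbers trained, delivering, stopped and interviewed. This also tells the planners of the full trial how many PWPs must be trained for each one who delivers.

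The cost is a few extra short interviews within a ceiling of 20 PWPs, and a small log. Some of those interviews will be with PWPs who did not deliver for neutral reasons and may add little. PWPs who have withdrawn remain free to decline, and the numbers declining should be shown.
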